### Data management

2.8

Suitably trained doctors will conduct face-to-face interviews with each patient to facilitate the completion of a questionnaire prior to undergoing assessments. The same doctors will then provide ongoing assistance to patients during subsequent visits, ensuring the avoidance of potential biases.

The data analysis for this study will be conducted on the Intranet computer, and the research and analysis dataset will be established based on the Intranet data analysis platform. Data sorting and analysis will be conducted by authorized researchers who are blinded to the assignment of study groups within the unit. All processes of data processing and analysis are documented, while preserving the original dataset.

### Descriptive statistics

2.9

The consistency analysis is conducted based on Gwet’s Agreement Coefficient 1 (AC1, 38) to assess the concordance between vibraimage technology and HADS detection results, as well as to determine the optimal threshold for vibraimage technology. Specifically, a HADS-A score of 8 or higher indicates anxiety, while a HADS-D score of 8 or higher suggests depression (10).

The measurement data that conform to a normal distribution are represented by *x̄* ± *s*, while the ones that do not conform are represented by the median (interquartile range). The difference between the two groups of measurement data following a normal distribution is assessed using a student *t*-test, whereas the difference between the two groups of measurement data not following a normal distribution is assessed using Mann–Whitney U test. The difference between the two groups is evaluated using *χ*^2^ test. Oneway-ANOVA analysis is employed for group comparisons. Pearson correlation analysis is used for measurement data with a normal distribution, and Spearman correlation analysis is used for measurement data without a normal distribution.

In the process of conducting binary logistic regression analysis to determine whether patients with FGIDs are also affected by psychological disorders, we will continuously enhance the model’s goodness of fit by eliminating irrelevant independent variables. Subsequently, a diagnostic model with high diagnostic efficiency will be derived. Finally, a Receiver Operating Characteristic (ROC) curve will be constructed based on the performance of sensitivity and specificity at various thresholds. This analysis will aid in identifying the optimal diagnostic test threshold and in evaluating the accuracy, sensitivity, and specificity of the test.

Variables with a *p* value <0.05 are considered statistically significant. The statistical analysis will be conducted by a medically trained personnel who will remain blinded to the assignment of study groups. The data statistics in our study will be conducted using paper questionnaires. In the event of missing items, we will either discard the questionnaire or, if necessary, employ imputation techniques to fill in the missing values.

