### Design

2.1

This is a prospective, observational, single-center trial. The patients with FGIDs will be continuously enrolled in the outpatient clinic by experienced physicians from the Department of Gastroenterology at Peking Union Medical College Hospital, who will strictly adhere to the guidelines. The diagnosis of FGIDs adheres to the diagnostic criteria outlined in Rome IV (1), encompassing primarily functional dyspepsia, irritable bowel syndrome, functional constipation, and other FGIDs. The diagnostic criteria for the aforementioned diseases are elaborated in the inclusion criteria. Baseline data including age, sex, marital status, employment status, body mass index (BMI), FGIDs subclasses, scores of symptoms and quality of life were recorded. The simultaneous evaluation of HADS and vibraimage technology will be conducted. The clinical screening efficacy of vibraimage technology will be assessed by comparing with HADS, which serves as the gold standard. The patients will be divided into two groups according to HADS, that is, FGIDs with or without psychological disorders. Both groups will be treated with identical conventional therapies. Post-treatment assessments of symptom questionnaire, HADS and vibraimage technology outcomes will be followed up, which may show the influence of psychological factors and provide a theoretical basis for the significance of identification and treatment of comorbid psychological disorders in FGIDs patients. The trial design is presented in Figure 1, while the subsequent sections provide a comprehensive and detailed description of our trial.

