### Sample size calculation

2.7

The sample size required for a trial comparing the efficacy of HADS and vibraimage technology in detecting comorbid psychological disorders in FGIDs patients is calculated here. Based on a literature search, it is evident that the prevalence of psychological disorders in FGIDs is 50%. Referring to previous methodological studies (22), we assume a sensitivity of 80% for vibraimage technology, a significance level (*α*) of 0.05, a test power (1 − *β*) of 0.8, and a margin error of 7%. Consulting relevant tables, we determine that the target sample size should be 251 individuals with an anticipated attrition rate of 10%, resulting in a final target sample size of 276 patients.

In addition, we conduct an analysis to determine the required sample size for the post-treatment follow-up experimental process in patients with FGIDs. Based on a literature review, the overall rate of improvement (P1) in FGIDs patients after receiving conventional treatment regimen is reported as 57% (37). We expect that patients with both FGIDs and psychological disorders will have an overall rate of improvement (P2) following conventional treatment at a ratio of 1: 2 compared to P1. The sample allocation between these two groups is set at 1: 1, with a test level *α* of 0.05, test efficacy (1 − *β*) of 0.8, and a loss rate of 10%. Through analysis using PASS software (V21.0.3), the target sample size is determined to be 98 individuals.

The specific distribution scheme of the sample can be observed in Figure 1.

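### Section 2.9 compares normally distributed scores between the HADS-defined groups with Student's equal-variance t-test, although neither equal group sizes nor equal spread is assured; Welch's test is the safer default

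*Protocol article*

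**What the plan says.** For two-group comparisons of continuous data, section 2.9 (Descriptive statistics) reads: "The difference between the two groups of measurement data following a normal distribution is assessed using a student" t-test. Data judged non-normal go to the Mann–Whitney U test. The section says nothing about equal or unequal variances. A p "value <0.05 are considered statistically significant".

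The groups are not randomised. Section 2.1 (Design) says "The patients will be divided into two groups according to HADS", and section 2.9 supplies the cut-offs: "a HADS-A score of 8 or higher indicates anxiety, while a HADS-D score of 8 or higher suggests depression". On recruitment, section 2.1 says "The patients with FGIDs will be continuously enrolled in the outpatient clinic". The visible text sets no quota per group.

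Section 2.7 (Sample size calculation) takes it that "the prevalence of psychological disorders in FGIDs is 50"%, and for the follow-up comparison says "The sample allocation between these two groups is set at 1: 1". It refers to Figure 1, which is not shown, for how the sample is distributed.

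**The concern.** Student's t-test uses one pooled variance for both groups. This is safe if the groups have equal variances or equal sizes. Section 2.9 checks neither: a normality check says nothing about equal variance. The sizes will be whatever the HADS results produce, because consecutive enrolment does not fix them.

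If sizes and variances both differ, the pooled standard error is biased. It is too small when the smaller group varies more, so differences are called significant too often and intervals are too narrow. It is too large when the smaller group varies less, with the reverse effect. The comparisons exposed are the normally distributed baseline and secondary scores, such as SF-36, HADS, any continuous vibraimage score, and symptom scores where they are analysed as continuous.

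**Working it through.** **Inputs from the protocol article**
- Target enrolment 276, attrition 10%, prevalence 50%, allocation 1:1 (section 2.7).
- Significance level 0.05 (section 2.9). Two-sided testing is assumed, since sidedness is not stated.

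**Inputs assumed**
- Evaluable patients: 276 × 0.9 = 248.4, taken as 248, all entering the group comparison.
- SD ratio between groups: 1.5 as an illustration, with smaller ratios for comparison. The documents give no SD for any score.

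**Step 1. The plan's own figure.** Section 2.7 takes improvement of 57% against half of that, 28.5%. With unpooled variance, two-sided 0.05 and power 0.80:

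n per group = (1.96 + 0.8416)² × (0.57 × 0.43 + 0.285 × 0.715) / 0.285² = 43.4, so 44.

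44 / 0.9 = 48.9, so 49 per group and 98 in total. This matches the stated 98. The calculation rests on equal groups and a binary endpoint.

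**Step 2. Real error rate of the pooled test (large sample).**

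V_true = s1²/n1 + s2²/n2

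V_pooled = [((n1 − 1)s1² + (n2 − 1)s2²)/(n1 + n2 − 2)] × (1/n1 + 1/n2)

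Error = 2 × (1 − Φ(1.96 × √(V_pooled/V_true)))

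Example: 99:149 with SD 1.5 in the smaller group and 1 in the larger.
- V_true = 2.25/99 + 1/149 = 0.02944.
- Pooled variance = (98 × 2.25 + 148 × 1)/246 = 1.498.
- V_pooled = 1.498 × (1/99 + 1/149) = 0.02518.
- √(0.02518/0.02944) = 0.925, and 1.96 × 0.925 = 1.813. Error = 7.0%.
- With the larger SD in the larger group, the factor is 1.081 and the error is 3.4%.

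| Split | SD ratio | Smaller group more variable | Larger group more variable |
|---|---|---|---|
| 124:124 | any | 5.0% | 5.0% |
| 109:139 | 1.25 | 5.6% | 4.4% |
| 109:139 | 1.5 | 6.1% | 4.0% |
| 99:149 | 1.25 | 6.1% | 4.0% |
| 99:149 | 1.5 | 7.0% | 3.4% |
| 74:174 | 1.5 | 9.4% | 2.2% |

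**Step 3. How likely are these splits?** With 248 patients and true prevalence 50%, the 95% binomial range for one group is 109 to 139. A split at least as uneven as 99:149 has probability about 0.2%. Such a split therefore points to a prevalence other than 50%. If only 98 patients were compared, the 95% range would be 39 to 59, so about 40:60 could arise by chance.

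**Step 4. Does the HADS cut itself make the spreads differ?** In a bivariate normal model with one cut, the SD ratio is 1.00 for a score unrelated to HADS and 1.00 at any correlation when the cut is 50:50. It is 0.97 to 0.99 at 40:60 and 30:70 with correlation 0.3 to 0.5. At a ratio of 0.97 or its inverse, the error is 4.9% to 5.1% at 99:149 and 4.7% to 5.3% at 74:174. If a patient is positive on either subscale, the ratio is about 0.92 to 1.26 for a HADS subscale, but 0.97 to 1.00 for a score correlated 0.5 with HADS.

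**Step 5. Welch's test.** In simulation under equal means (100,000 runs per cell, N = 98 and 251, smaller-group share 20% to 50%, SD ratio 0.5 to 2), Welch's test had an error of 4.9% to 5.2% in every cell. Student's test held 4.9% to 5.2% at an even split. At 40:60 it ranged from 2.7% to 8.5%.

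**The case against.** A reader might infer that splitting on HADS necessarily makes variances unequal, so that the stated 5% is already lost. The documents do not support that. They give no SDs, and step 4 shows that the cut alone leaves spreads equal or nearly so for scores unrelated or moderately related to HADS. An SD ratio of 1.5 is an illustration, not something derived from the plan.

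It is also fair to say that the plan assumes 50% prevalence and 1:1 groups, and that Student's test is sound at that split. The larger distortions need both a real departure from that prevalence and clearly different spreads. The 248 is uncertain too, since section 2.7 sizes the follow-up comparison at 98 and Figure 1 is not visible.

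The scope is narrow. Sensitivity and specificity (2.6.1) and the improvement proportion (2.6.2) are not t-tested. The abstract defines the symptom-score endpoint as a reduction of more than 50%, which is binary, although 2.6.2 speaks of a degree of improvement. For scores correlated with HADS the group means will differ anyway, so type I error is hardly the issue there; the width of the confidence interval still is.

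Finally, Student's name may be shorthand in a condensed article, with the variance option settled in an analysis plan that is not shown.

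Most of this stands and limits the size of the point. It does not remove it. The article names a specific test whose only stated condition is normality, for groups whose sizes are not controlled.

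**Conclusion.** The point holds as a minor, conditional improvement, not as a demonstrated failure of the error rate. Section 2.9 fixes a test that depends on equal variances or equal sizes, and the design guarantees neither. At an even split there is no distortion.

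For 248 patients within the chance range around 50% prevalence, an SD ratio of 1.5 would put the real error between 4.0% and 6.1%. At 40:60 it would be 3.4% to 7.0%, and the nominal 95% interval would cover about 93.0% to 96.6% of the time. If the spreads are nearly equal, the error stays close to 5%. These figures rest on the assumed SD ratio, the assumed 248 patients and two-sided testing. Only normally distributed baseline and secondary continuous scores are affected.

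**What to change.** In section 2.9, name Welch's t-test in place of Student's for the normally distributed two-group comparisons, and report each mean difference with its Welch 95% confidence interval. Leave the Mann–Whitney provision as it is. No change to the regression text is needed on this account: the only regression there is a logistic model with psychological disorder as the outcome. If Welch's test is already intended, naming it settles the ambiguity.

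The cost is a small wording change and no extra data. The loss of efficiency is negligible if the variances turn out equal.

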**Methods:**

This is a prospective, single-center observational trial. 276 FGIDs outpatients who visit Peking Union Medical College Hospital will be evaluated simultaneously by HADS and vibraimage technology, then to evaluate the screen efficacy of this technology. The patients will be allocated into two groups (those with or without psychological disorders). The primary endpoint is the overall rate of improvement, specifically referring to the proportion of patients who achieved Likert scores greater than or equal to 4. The secondary endpoints encompass evaluating whether there is a reduction of more than 50% in symptom evaluation scores such as IBS-SSS. Additionally, the study will assess changes in health status and quality of life using SF-36 questionnaires and the patients’ satisfaction with treatment. Furthermore, psychological status will be reassessed by vibraimage technology and HADS after treatment to evaluate the effect of combined psychological factors on FGIDs treatment.

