### Conventional treatment

2.5

Patients enrolled in the study with FGIDs will receive conventional specialty care in gastroenterology. The clinician needs to determine which symptom features are dominant, and which treatment (s) are most likely to lead to improvement. Certain patients may find simple, cost-effective interventions such as laxatives or anti-diarrheal medicine (2). Treatment principles for patients with the same subtype of FGIDs are consistent, but actual treatment plans may vary slightly based on individual patient circumstances. The conventional treatment in this study does not encompass the utilization of psychotherapeutic drugs and psychotherapy.

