#### The assessment of patient prognosis and satisfaction

2.6.2

The patients will be divided into two groups according to HADS, that is with or without psychological disorder group. The patients in both groups will receive the conventional treatment, without any additional interventions beyond the standard care for FGIDs. The treatment effect questionnaire will be administered after 4 weeks. Overall improvement will be evaluated using a 5-point Likert scale (36), where patients will be prompted to complete the following statement: “How does my gastrointestinal condition compare to before I commenced treatment at the clinic?” The response options include: deteriorated, slightly deteriorated, unchanged, slightly improved, and significantly improved. The HADS and vibraimage technology will also be systematically evaluated.

Primary endpoint: the overall rate of improvement, specifically referring to the proportion of patients who achieved Likert scores greater than or equal to 4.

Secondary endpoint: HADS and vibraimage technology outcomes, along with the improvement degree of FGIDs symptom scores such as IBS-SSS, quality of life by SF-36 questionnaires, and the patients’ satisfaction with treatment.

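### The improvement rate is compared between non-randomised HADS groups with, as far as stated, only an unadjusted chi-square test, so differences in subtype or case mix may be read as an effect of psychological comorbidity

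*Protocol article*

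**What the plan says.** - **Design (2.1).** "This is a prospective, observational, single-center trial". The groups come from a questionnaire result: "The patients will be divided into two groups according to HADS, that is, FGIDs with or without psychological disorders". The same section says of treatment: "Both groups will be treated with identical conventional therapies".
- **Primary endpoint of the prognosis part (2.6.2).** "the overall rate of improvement, specifically referring to the proportion of patients who achieved Likert scores greater than or equal to 4", assessed after 4 weeks.
- **Analysis (2.9).** Measurement data get a t-test or Mann–Whitney test. Then: "The difference between the two groups is evaluated using" a chi-square test. The only regression in the section is a "binary logistic regression analysis to determine whether patients with FGIDs are also affected by psychological disorders". Its outcome is psychological disorder, not improvement.
- **Treatment (2.5).** Principles are consistent within a subtype, but "actual treatment plans may vary slightly based on individual patient circumstances".
- **Purpose.** Section 2.1 expects the post-treatment assessments to show how psychological factors influence the result. The Abstract (Methods) says the reassessment of psychological status is "to evaluate the effect of combined psychological factors on FGIDs treatment".
- **Baseline data (2.1, 2.3).** Age, sex, FGID subclass, symptom scores and course of illness are recorded. No use of them is stated for the improvement comparison.

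**The concern.** HADS-positive and HADS-negative patients may differ in more than psychological status. The study pools functional dyspepsia, irritable bowel syndrome, functional constipation and other FGIDs. If subtype predicts improvement at 4 weeks and the subtype mix differs between the groups, the crude difference contains a subtype component. Because treatment follows subtype, a difference in mix is also a difference in treatment. Age, sex and other case-mix variables can act in the same way.

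An unadjusted test cannot separate these components. At stake is the second aim of the study: a lower improvement rate in HADS-positive patients could be reported as the influence of psychological factors when part of it reflects who those patients are. The limitations in section 3 do not mention confounding.

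**Working it through.** **1. The plan's own figure.** Inputs from section 2.7: P1 = 0.57; P2 half of that, 0.285; 1:1 allocation; alpha 0.05 (two-sided assumed); power 0.80; loss 10%. With the unpooled normal approximation:

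n per group = (1.960 + 0.842)² × [0.57 × 0.43 + 0.285 × 0.715] / 0.285² = 7.85 × 0.4489 / 0.0812 = 43.4, rounded up to 44.

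Total 88; 88 / 0.9 = 97.8, rounded up to 98. The stated 98 is reproduced. The comparison is sized as a crude test of two proportions, with a planned difference of 57 − 28.5 = 28.5 points.

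**2. Which method applies to the endpoint.** The endpoint is binary and the groups are two. The t-test and Mann–Whitney test are for measurement data, one-way ANOVA and the correlations do not fit, and the logistic regression has another outcome. The chi-square test remains, by elimination. No strata, covariates, matching or weights are stated for it.

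**3. How large the bias could be.** The documents give no imbalance, so every stratum value here is assumed. Take two strata of equal size, A (better outlook) and B (worse outlook), with no effect of psychological status inside either. The crude difference is then

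(comorbidity in B − comorbidity in A) × (improvement in A − improvement in B).

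| Comorbidity A / B | Improvement A / B | Crude difference | Share of 28.5 |
|---|---|---|---|
| 50% / 50% | any | 0 | 0% |
| 40% / 60% | 67% / 47% | 0.20 × 0.20 = 4 points | 14% |
| 35% / 65% | 72% / 42% | 0.30 × 0.30 = 9 points | 32% |

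By normal approximation, a nominal 5% chi-square test would then reject in about 7% (4 points) and 14% (9 points) of studies with 44 per group, and in about 10% and 30% with 124 per group. With an equal mix the rate stays at 5%. The formula also shows that the sign can reverse: if comorbidity is commoner in the better stratum, the crude test understates the association.

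**4. How many covariates the data can carry.** Average improvement at the planned rates is (0.57 + 0.285) / 2 = 0.4275. Four subtype classes need 3 terms. The core model (HADS group, subtype, age, sex) has 1 + 3 + 1 + 1 = 6 terms; adding severity and illness duration gives 8.

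| Follow-up | Evaluable | Improved | Per term, 6 terms | Per term, 8 terms |
|---|---|---|---|---|
| All 276 | 276 × 0.9 ≈ 248 | 248 × 0.4275 ≈ 106 | 17.7 | 13.3 |
| Target of 98 | 88 | 88 × 0.4275 ≈ 38 | 6.3 | 4.8 |

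Sections 2.1 and 2.6.2 describe follow-up of both groups without naming a subset. Section 2.7 gives this comparison its own target and refers to Figure 1, which is not available here, for the distribution. Both cases must therefore be kept open.

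**The case against.** **The analysis plan may settle this.** A condensed article need not list covariates, and the chi-square sentence names no endpoint. Both points are fair, and the link to the improvement rate is by elimination. But the article does list its tests, and gives a regression only for a different question. The stated method does not match the stated purpose, which is more than an omitted detail.

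**The aim may be descriptive.** The Abstract speaks of observing outcomes with and without comorbidity, and for a purely prognostic question a crude comparison is legitimate. The effect wording in the Abstract is also attached to the reassessment of psychological status rather than to the Likert endpoint. This stands in part: the crude result should be kept. It does not remove the point, because section 2.1 expects the symptom follow-up itself to show the influence of psychological factors.

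**Treatment is protected.** Under section 2.3 the physicians do not know the HADS or vibraimage results, psychotherapeutic drugs and psychotherapy lie outside conventional treatment, and plans are said to vary only slightly. A reader might infer that HADS status steers prescribing; the documents do not support that. Blinding limits prescribing driven by HADS, but not confounding through subtype, age or other case mix.

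**Severity may be a mediator.** Distress may worsen symptoms, so adjusting for baseline severity could remove part of the effect sought. This stands, and severity should not enter the only adjusted model.

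**Conclusion.** The point holds in a limited form. Groups classified by baseline HADS are compared on a binary endpoint, the only stated method that fits is unadjusted, and the conclusion sought goes beyond description. The comparison is open to confounding by subtype and case mix, which data already collected could reduce.

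Stronger readings are not supported:

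- The groups are not self-selected. Patients are classified by score.
- It cannot be said that the result will be biased, or by how much. The 4 to 9 points rest wholly on assumed strata; even there they are at most about a third of the planned 28.5, so they would not by themselves produce the planned effect.
- It cannot be said that the baseline variables go unused altogether. The predictors of the diagnostic regression are not named and may include them; only their use in the improvement comparison is unstated.
- It cannot be assumed that a model with about 8 terms is affordable. That depends on whether 276 or 98 patients are followed.

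**What to change.** 1. **Add a prespecified adjusted analysis of Likert ≥4:** logistic regression on HADS group with FGID subtype, age and sex. Report the adjusted odds ratio and the standardised risk difference with 95% confidence intervals, beside the crude chi-square result.
2. **Add a second model** with baseline severity and illness duration. Section 2.3 uses different symptom scales by subtype, so standardise severity within instrument. State that severity may lie on the pathway from distress to outcome.
3. **State how many patients enter the follow-up comparison,** and match the number of terms to it. With about 38 improved patients even the 6-term model is thin, and fewer terms would be needed.
4. **Tabulate the treatment received by HADS group,** and reconcile the treatment descriptions in sections 2.1 and 2.5. The sponsor must decide which describes the study.
5. **Name residual confounding as a limitation** in section 3.

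The covariates are already collected, so the cost is protocol wording, slightly more analysis and a somewhat less simple primary result. The models should be fixed before outcomes are examined by group, since covariates chosen afterwards carry less weight.

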Human micromovements, also known as vibrations, can be measured using standard digital, network or television cameras and image processing technologies. These movements are closely linked to the human vestibulo-emotional reflexes (VER) and can reflect emotional states and personality traits (28). By detecting three-dimensional (3D) head and neck movements over several video frames, fluctuations in emotions can be identified (29). As depicted in Figure 2, each pixel of a video image represents a vibration parameter such as frequency or amplitude. The visualization of these parameters is called an external vibration image (30) which resembles a vibratory halo around the person’s head. Generally, the color of this image corresponds to the vibration frequency while its size reflects the amplitude. This mapping of micro-changes to individuals’ psychological states allows for the development of a video-based psychological assessment method. Currently, this technology can give assessment reports of patients’ psychological status, for example, whether they have anxiety or depression status. The primary application of this technology lies in the realm of public safety, encompassing lie detection and human-computer interaction systems (31–34). Furthermore, it holds significant potential for clinical disease diagnosis, particularly in cases related to depression (35). The patients diagnosed with FGIDs will be instructed to assume an upright position, facing the camera, for approximately three minutes of video recording.

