#### The evaluation metric for the diagnostic test

2.6.1

Primary Outcome: Sensitivity and specificity of vibraimage technology compared to HADS as the gold standard.

Secondary Outcomes: Positive predictive value (PPV), negative predictive value (NPV), and overall accuracy of vibraimage technology.

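### The vibraimage threshold is chosen and its sensitivity and specificity are evaluated in the same patients with no validation step, so the primary accuracy figures will be modestly optimistic

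*Protocol article*

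**What the plan says.** Section 2.6.1 gives the primary diagnostic outcome as "Sensitivity and specificity of vibraimage technology compared to HADS as the gold standard". All patients belong to one single-centre cohort and "will be evaluated simultaneously by HADS and vibraimage technology" (Abstract, Methods; also section 2.1).

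Section 2.9 then describes three data-driven steps in that cohort:

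- Gwet's AC1 is used to assess agreement with HADS, "as well as to determine the optimal threshold for vibraimage technology".
- A binary logistic regression for psychological disorder is refined to improve its "goodness of fit by eliminating irrelevant independent variables". The candidate variables are neither named nor counted. "Subsequently, a diagnostic model with high diagnostic efficiency will be derived".
- An ROC curve is built, of which the section says: "This analysis will aid in identifying the optimal diagnostic test threshold and in evaluating the accuracy, sensitivity, and specificity of the test".

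The article mentions no pre-set vibraimage cut-off, split sample, cross-validation, bootstrap correction or external sample. Section 2.4 says that "this technology can give assessment reports of patients" on psychological status, "for example, whether they have anxiety or depression status". No section says that this output, at a locked cut-off, is the test evaluated for the primary outcome.

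**The concern.** A threshold picked because it performs best in a sample performs better in that sample, on average, than it will in new patients. Reading sensitivity and specificity off the same ROC curve that selected the threshold therefore gives estimates biased upward. Ordinary confidence intervals also ignore the selection, so they are too narrow. If a multivariable model is fitted to the same patients first, its coefficients add further optimism.

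The blinding in sections 2.3, 2.8 and 2.9 does not prevent this. It keeps the two assessments and the analyst apart, but the threshold is still fitted to HADS status at the analysis step.

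At stake is the main diagnostic result. A screening tool could be reported as somewhat more accurate, and more precisely measured, than it will prove in later use.

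There is also an ambiguity of target. Section 2.9 offers two threshold rules (AC1 and ROC) and possibly two classifiers (vibraimage alone, or a logistic model with other variables). It does not say which supplies the primary figures.

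**Working it through.** **1. The plan's own figure.** Inputs from section 2.7: assumed sensitivity 80%, prevalence 50%, α 0.05, margin 7%, attrition 10%.

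- HADS-positive patients needed: 1.96² × 0.8 × 0.2 / 0.07² = 125.4.
- Total: 125.4 / 0.5 = 250.9, so 251, as stated.
- With attrition: 251 × 1.1 = 276.1, so 276, as stated.

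This is the precision formula for a single proportion. It treats sensitivity as measured at a cut-off fixed in advance and makes no allowance for choosing the cut-off on the same patients.

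**2. Threshold choice alone.** Simulation with 251 patients and 50% prevalence. Scores are normal with SD 1, mean 0 in HADS-negatives and mean d in HADS-positives. For true 80%/80%, d = 2 × Φ⁻¹(0.80) = 1.683; for 70%/70%, d = 2 × Φ⁻¹(0.70) = 1.049. In each of 4,000 data sets the cut-off c maximises either sensitivity + specificity (the Youden index) or AC1. Apparent accuracy is then compared with true accuracy at that same c: sensitivity 1 − Φ(c − d), specificity Φ(c). Mean inflation in percentage points (columns rounded separately):

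| True Se/Sp | Rule | Sensitivity | Specificity | Sum |
|---|---|---|---|---|
| 80/80 | Youden | 2.1 | 2.0 | 4.2 |
| 80/80 | AC1 | 2.1 | 2.0 | 4.1 |
| 70/70 | Youden | 2.5 | 2.4 | 4.9 |
| 70/70 | AC1 | 2.6 | 2.7 | 5.3 |

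A separate run with groups of 125 and 126 at 80/80 gave about 2.2 points for sensitivity and 1.9 for specificity. Against the margin for sensitivity: 2.1 / 7 = 30%, or 2.2 / 7 = 31%.

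**3. Interval coverage.** At 80/80, the ordinary 95% Wald interval for sensitivity covers the true value at the chosen cut-off in about 89% of data sets (about 87% in the separate run). At a fixed cut-off the figure is about 94%. For sensitivity + specificity − 1, coverage at the chosen cut-off is about 86%.

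**4. If a logistic model supplies the figures.** Assumed: one informative variable, the rest noise, backward elimination at p < 0.05, then a Youden cut-off, evaluated on 20,000 new patients (400 runs per setting). Inflation of the sum:

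| True Se/Sp | 5 candidates | 10 | 20 |
|---|---|---|---|
| 80/80 | 4.5 | 5.1 | 6.7 |
| 70/70 | 5.6 | 6.2 | 8.6 |

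Comparison with keeping every candidate in the model (separate run, 80/80): with 10 candidates the sum is inflated by 8.1 points in the full model and 5.0 after elimination; with 20, by 13.0 and 7.2. The number of candidates drives the optimism, and elimination reduces it relative to the full model.

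**5. Two threshold rules.** At 50% prevalence AC1 and Youden give similar cut-offs on average. At an assumed 30% prevalence and d = 1.683 they diverge: mean apparent sensitivity/specificity is 82.1%/81.2% with Youden and 59.9%/94.0% with AC1. The primary result can therefore depend on which rule is used.

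**The case against.** The strongest reply has three parts. The stated aim in the Abstract is to explore the technology, and no accuracy success criterion or hypothesis test is set, so no decision rule is corrupted. The bias from the threshold is small, about 2 points per measure. And internal validation is the sort of detail that an analysis plan, not shown here, could supply.

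The first two parts stand and limit the severity. The third stands only in part. Section 2.9 is not merely silent: it assigns threshold selection and accuracy evaluation to the same analysis in the same patients. A later plan would have to amend that.

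Several stronger readings are tempting but not supported:

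- *The bias uses up much of the 7-point margin.* The margin applies to sensitivity alone, so the comparison is about 2 points with 7, under a third. The 4-point figure is the sum of two measures.
- *Eliminating variables makes optimism worse.* It does so only against a single pre-chosen score; against the full model it reduces optimism (step 4).
- *Dropping variables cannot improve fit.* True of the likelihood, but not of criteria such as AIC, BIC or Hosmer-Lemeshow. Section 2.9 names no criterion, so no error is shown.
- *The logistic model provides the primary figures.* Section 2.9 never says so. The sentence that ties a data-chosen threshold directly to vibraimage is the one on AC1.
- *A ready classification exists that needs no tuning.* Section 2.4 says only that the technology can issue reports. It gives no cut-off or version, and section 2.9 treats the threshold as still to be determined.

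**Conclusion.** The point holds in a moderate form. As written, section 2.9 gives upwardly biased sensitivity and specificity for the primary diagnostic outcome, with intervals that are too narrow. From the threshold alone the inflation is about 2 points per measure at 80/80, with coverage for sensitivity of about 87-89%. If the figures come from the logistic model, the sum is inflated by about 5-7 points at 80/80 with 10-20 candidates.

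Only the 80% sensitivity and 50% prevalence come from the protocol. The 80% specificity, normal scores, candidate counts and single informative variable are assumptions. The bias is larger for a weaker test. At 30% prevalence with Youden, the sensitivity part rises to 3.2 points at 80/80 and 3.8 at 70/70. It would not arise if a cut-off locked beforehand were used, but the text says the threshold is to be found in the study. Severity: should-fix.

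**What to change.** In section 2.9, name one classifier (vibraimage alone) and one threshold rule as the source of the primary sensitivity and specificity. Then do one of the following:

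- If the technology's existing anxiety/depression output provides a cut-off, record it and lock it before HADS data are opened. Report sensitivity and specificity at that cut-off with 95% confidence intervals.
- If not, choose the threshold in the study, but report optimism-corrected sensitivity and specificity, with confidence intervals, from a bootstrap or cross-validation that repeats the threshold choice in every resample.

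Report the multivariable logistic model separately as a secondary analysis, listing its candidate variables. Apply the same correction, repeating any variable elimination as well as the threshold choice in every resample.

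The cost is some extra analysis work, and reported accuracy that is lower by a few points. No additional patients or data collection are needed.
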